## Methods

### Study aims

This study aims to determine the clinical outcomes of an acute STEMI within one year of clinical presentation to the division of cardiology at the CMJAH. The study also evaluates the association between baseline serum cardiac biomarkers of myocardial infarction and all-cause mortality within a year of acute STEMI.

The primary objective is:

To determine the all-cause mortality rate of an acute STEMI at 30 days, three and six months, and one year after the index presentation.

The secondary objectives include:

To determine the rates of cardiac-related re-hospitalisation, heart failure, angina, major bleeding, thromboembolism, non-fatal arrhythmias (namely, atrial fibrillation, ventricular tachycardia, and complete heart block) and planned or unplanned repeated revascularisation at 30 days, three and six months and one year after the index STEMI at CMJAH.To assess the relationship between all-cause mortality and the peak serum hs-cTnT, CRP and SUA measured on admission.To describe the baseline clinical characteristics of STEMI patients in our setting.To compare the clinical outcomes between STEMI patients who received thrombolysis, PCI, a pharmaco-invasive strategy and those who underwent no reperfusion at 30 days, six and three months, and one year after the index STEMI.To determine the baseline clinical predictors of all-cause mortality at 30 days, three months, six months and one year after the initial STEMI.To describe the adjuvant medical care provided and medication compliance rates at 30 days, three months, six months and one year after the index discharge from the hospital.

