This study seeks to determine the event rates of crude mortality, crude survival, re-hospitalisation, heart failure, angina, major bleeding, thromboembolism, arrhythmias and revascularisation at 30 days, three months, six months and one year after the index STEMI. We seek to compare these clinical outcomes between four primary STEMI sub-groups (i.e., those who receive fibrinolysis vs. no fibrinolysis vs. PCI vs. no PCI) in our local practice and compared with those reported in HIC and other regions of SSA. We also aim to evaluate the association between the peak baseline measurements of serum hs-cTnT, serum CRP, SUA and clinical outcomes within a year.

We hypothesise that the thirty-day and one-year crude mortality rates for STEMI patients observed in our setting would follow similar trends to those in HIC with no significant differences. We anticipate that the various STEMI management therapies provided in our practice would offer similar one-year all-cause mortality and morbidity benefits, irrespective of the revascularisation strategy used when comparing fibrinolysis vs. PPCI vs. fibrinolysis followed by PCI among groups. In our setting, we expect that advanced age, female gender, diabetes mellitus and heart failure on admission play critical roles in predicting death at 30 days and one year.

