### Data collection

Research data will be collected from 01 May 2021 to 30 October 2022. The Primary Investigator (PI) will use the Research Electronic Data Capture (REDCap) software as the primary data collection tool. At baseline, the PI will capture demographic, clinical, calculated TIMI and GRACE scores, laboratory test results, ECG, echocardiographic, coronary angiographic, revascularisation and discharge medication data shown in Appendix B. The PI will create and access a reference list of the study participants’ hospital numbers and specific study numbers. The PI will retrieve these from the relevant progress notes, National Health Laboratory Service (NHLS) lab track, electronic medical records, and coronary angiogram report database of the division of cardiology at CMJAH.

The PI will telephonically contact all participants or their designated family members to monitor general well-being, medication compliance, outpatient cardiac clinic visits and cardiac-related re-admissions. When re-admitted to CMJAH, the PI will access the relevant hospital records to ascertain whether our study’s outcomes of interest occurred. Participants will be deemed compliant with medication if they say so during the telephonic interviews. The telephonic interviews will follow a closed-ended structured questionnaire, as depicted in Appendix C. Each participant will receive a telephonic interview call at 30 days, three months, six months and twelve months after the index hospital discharge date. All participants will be given the PI’s phone number and business card and encouraged to save the number on their cellphones when they sign informed consent forms so that doctors from other hospitals can contact the PI for cardiac-related referrals to CMJAH.

The PI will obtain the peak values of serum hs-cTnI, serum CRP and SUA from routine blood tests drawn at baseline for all participants. Automated messages generated through REDCap will be sent to remind both the PI and the participants of their scheduled outpatient clinic visits a week before the visits.

An experienced research sonographer will perform standardised echocardiograms during the outpatient clinic visits three months and one year after the index discharge. The two cardiologists who supervise the study will verify all echocardiograms. Appendix D shows the left ventricular parameters and valve analysis that will be recorded.

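### Follow-up calls are described as tracking cardiac-related re-admissions, so admissions for major bleeding or thromboembolism may be missed, mainly at other hospitals

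*Protocol article*

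**What the plan says.** **Outcomes.** The secondary objectives in Study aims open with "To determine the rates of cardiac-related re-hospitalisation, heart failure, angina, major bleeding, thromboembolism" and go on to non-fatal arrhythmias and repeat revascularisation, all at 30 days, three months, six months and one year. Re-hospitalisation is restricted to cardiac causes. Major bleeding and thromboembolism are separate items with no such restriction. A further secondary objective compares clinical outcomes between thrombolysis, PCI, pharmaco-invasive and no-reperfusion patients.

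**Background wording.** The last part of the Background lists "event rates of crude mortality, crude survival, re-hospitalisation, heart failure, angina, major bleeding, thromboembolism, arrhythmias and revascularisation", with no cause attached to re-hospitalisation.

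**Ascertainment.** Under Data collection, the PI telephones participants or designated family members to "monitor general well-being, medication compliance, outpatient cardiac clinic visits and cardiac-related re-admissions". On the instrument: "The telephonic interviews will follow a closed-ended structured questionnaire, as depicted in Appendix C". On records: "When re-admitted to CMJAH, the PI will access the relevant hospital records to ascertain whether" the study's outcomes took place. On other hospitals: participants carry the PI's number "so that doctors from other hospitals can contact the PI for cardiac-related referrals to CMJAH". Clinic visits at three months and one year are described as the occasion for echocardiograms.

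**Acknowledged limitation.** The Discussion accepts that telephone follow-up may lead patients to leave out health information, and so to under-reporting of cardiovascular events.

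**The concern.** An outcome can be counted only if some route brings it to the study's attention. Two listed outcomes, major bleeding and thromboembolism, can put a patient in hospital for a reason that a lay person would not call cardiac: a gastrointestinal bleed, for example, or a clot in a limb. The re-admission item of the calls is described as cardiac-related, and the person answering may be a relative. If the question is put that way, the respondent decides what counts as cardiac before the PI sees any record, and a truthful answer may leave out exactly the admission that the study needs.

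The events at stake are the main safety outcomes in the comparison of reperfusion strategies. The Background anticipates similar morbidity across strategies, so a low count of bleeds or emboli would be easy to read as support for that expectation when it may partly reflect how events were sought.

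The gap is also one-directional. Cardiac re-admission can be derived from a list of all admissions, but bleeding and embolic admissions cannot be recovered from a list of cardiac ones.

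**Working it through.** The article gives no rate of re-admission, bleeding or thromboembolism, and the plan has no figure of its own to reproduce. The check is therefore a tracing exercise: take each ascertainment route in Data collection and ask whether it would pick up a bleed or an embolus.

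| Route described | Cause restriction | Place restriction | Finds a non-cardiac bleed or embolus? |
|---|---|---|---|
| Call: re-admission item | Cardiac-related | None | Only if the respondent regards it as cardiac |
| Call: general well-being item | None | None | Possibly; neither event is named |
| Record check | None (study outcomes) | CMJAH only | Yes, once the PI knows of the re-admission |
| Contact from outside doctors | Cardiac-related referrals | Other hospitals | Not as described |
| Clinic visits at three months and one year | Not described as event ascertainment | Clinic | Possibly |
| Appendix C questionnaire | Not shown | Not shown | Unknown |

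Three cases follow from the table.

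1. **Cardiac re-admission at another hospital.** The call item covers it, and so may the referral route. There are two described routes.
2. **Bleed or embolus admitted to CMJAH.** The record check is not limited to cardiac admissions, and both events are study outcomes. It is covered, provided that the PI learns of the admission. The article does not say how, apart from the calls.
3. **Bleed or embolus admitted to another hospital and not regarded as cardiac.** The call item and the referral route are both cardiac-related, and the record check does not reach the hospital. What remains is an answer about general well-being, a remark at a clinic visit, or a question in Appendix C that cannot be seen.

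The gap is therefore concentrated in the third case.

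**Effect on the group comparison.** Let the true event risks in two groups be p1 and p2, and let a share s of true events be found, with no false positives. If s is the same in both groups:

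- observed ratio: (s × p1)/(s × p2) = p1/p2, unchanged;
- observed difference: s × p1 − s × p2 = s × (p1 − p2), smaller by the factor s.

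Equal loss thus shrinks absolute differences and leaves fewer events for any test, but does not bias the risk ratio. If the shares differ, say s1 and s2, the observed ratio is (s1/s2) × (p1/p2), which can move either way. The article gives no basis for s, s1 or s2.

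**Re-hospitalisation wording.** The Background says re-hospitalisation without a cause; Study aims and Data collection both say cardiac-related. The Background also shortens other items in the same list: arrhythmias and revascularisation appear there without the qualifiers that Study aims gives them. This is abbreviation and not a competing definition, although the text shown does not define what cardiac-related means.

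**The case against.** The strongest case against is that the instrument itself is not shown. The article summarises the calls in four items, does not say that the summary is exhaustive, and refers to Appendix C for the questions. Appendix C may ask directly about bleeding, stroke, clots or any admission. What an article leaves to its appendices cannot be called missing. This stands, and it is why the point is conditional: events may be missed, and no more than that can be said.

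A second argument is that the record check at CMJAH has no cardiac restriction, that general well-being is asked about, and that there are two clinic visits. This also stands. A reader might infer that the loss applies equally at the study hospital, or that these admissions simply drop out of the data. The text does not support either inference.

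A third is that the authors already acknowledge under-reporting by telephone. This answers the point only in part. Their limitation concerns respondents who omit information. Here the respondent may answer the described item correctly and the event still goes unrecorded, which can be avoided by asking a wider question.

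A fourth is that the Background wording is shorthand. This is accepted: on its own the mismatch is clerical. A reader might infer that an all-cause re-hospitalisation outcome was promised and cannot be computed, but the formal objective is cardiac-related and the data collection agrees with it.

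**Conclusion.** The stated scope of follow-up is narrower than the list of secondary outcomes. As described, an admission to another hospital for major bleeding or thromboembolism that the patient or relative does not regard as cardiac has no clear route into the data. Under-ascertainment is a real risk there and a lesser one at CMJAH.

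The size cannot be calculated. One could assume that 3% to 10% of 355 patients have a non-cardiac re-admission within a year, which gives 355 × 0.03 ≈ 11 to 355 × 0.10 ≈ 36 patients. A reader might take this as the number of lost events, but it would not be one. The percentages are not in the article, nothing indicates how many such admissions would be bleeds or emboli, and those at CMJAH are open to the record check.

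A reader might also infer a bias towards similar reperfusion groups through differing antiplatelet exposure. The article reports no exposure by group, and its Background says dual antiplatelet therapy is recommended for all STEMI patients. Equal loss would shrink absolute differences but not risk ratios, and unequal loss has no known direction.

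The conclusion assumes that Appendix C does not already ask about these events or about admissions of any cause. If it does, what remains is to say so in Data collection and to tidy the Background wording.

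**What to change.** - Unless Appendix C already does so, ask at each call whether the participant has had any hospital admission since the last contact, and record the date, hospital and stated reason.
- Have the PI classify each admission as cardiac, bleeding, thromboembolic or other, and give a working definition of cardiac-related.
- Keep cardiac-related re-hospitalisation as the secondary outcome in Study aims, derived from these data. Align the re-hospitalisation item in the Background with it, and describe the wider question in Data collection.
- If Appendix C already covers this, one sentence in Data collection saying so is enough.

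The cost is one question in an existing structured call, one cause field in REDCap and a few more admissions to classify. No extra visits or staff are needed. For calls already made, the question can be asked retrospectively at the next scheduled contact, with some loss of recall.

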#### Characteristics of study participants

All consecutive patients presenting to CMJAH with an acute STEMI diagnosis will be invited to participate in the study as shown in the flow diagram provided in Appendix A.

Inclusion criteria include:

Age ≥ 18 years.All confirmed acute STEMI diagnoses as per the fourth universal definition of myocardial infarction, i.e., myocardial injury evidenced by a rise and/or fall of serum cardiac troponin levels with at least one value above the 99th percentile of the upper reference limit, in the presence of the following, ischaemic symptoms and new ischaemic ECG changes, i.e., persistent ST-segment elevation of at least 1 mm measured from the J-point in at least two contiguous leads, or new pathological Q-waves or a new-onset left bundle branch block.All confirmed STEMI receiving the various STEMI management, i.e., thrombolysis, PCI, pharmaco-invasive approach, and no reperfusion.Able to give written informed consent.The participant or participant’s next of kin is reachable by cellphone.

Exclusion criteria include:

ACS other than STEMI, i.e., NSTEMI and unstable angina.Unable to give consent.Unreachable by telephone call (participant or their next of kin).Incomplete medical records.

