### Statistical analysis

Stata Corp. IC Version 16.1 will be used for all statistical analyses. Normally distributed continuous data will be presented as means with standard deviations (± SD). Continuously skewed data will be reported as medians with interquartile ranges (IQR). We will express categorical data as numbers and percentages. For intergroup comparisons, the student’s unpaired t-test and one-way analysis of variance (ANOVA) with Fisher’s test will be used for continuous variables and the chi-square test for categorical variables. Demographic and clinical profiles will be presented in frequency tables. Univariate and multivariate cox regression analyses will be used to determine the baseline clinical predictors of mortality. Survival curves generated by the Kaplan-Meier method will be used to determine the crude one-year survival among the different reperfusion groups and compared with log-rank tests. All variables will be expressed with their hazard ratio and 95% confidence intervals. For all tests, a p-value < 0.05 will be considered statistically significant.

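### The only stated between-strategy test for heart failure and arrhythmia outcomes is an unadjusted chi-square, so admission case mix alone can make the reperfusion groups differ

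*Protocol article*

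**What the plan says.** Under Study aims, a secondary objective begins "To determine the rates of cardiac-related re-hospitalisation, heart failure, angina, major bleeding, thromboembolism, non-fatal arrhythmias (namely, atrial fibrillation" and adds ventricular tachycardia, complete heart block and repeat revascularisation, each at 30 days, three, six and twelve months. The Background introduces the same outcomes: "This study seeks to determine the event rates of crude mortality, crude survival, re-hospitalisation, heart failure, angina, major bleeding". A separate objective compares clinical outcomes between patients given thrombolysis, PCI, a pharmaco-invasive strategy or no reperfusion. No qualifier such as new, incident or worsening is attached to heart failure, angina or the arrhythmias.

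The Background also treats heart failure as an entry characteristic: "we expect that advanced age, female gender, diabetes mellitus and heart failure on admission play critical roles in predicting death". The exclusion list is "ACS other than STEMI, i.e., NSTEMI and unstable angina.Unable to give consent.Unreachable by telephone call (participant or their next of kin).Incomplete medical records". It removes nobody for earlier heart failure, stable angina or atrial fibrillation.

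For comparisons between groups, the Statistical analysis section says that the t-test and ANOVA "will be used for continuous variables and the chi-square test for categorical variables". Multivariable Cox regression is given for predictors of mortality, and Kaplan-Meier curves with log-rank tests for survival by reperfusion group. No adjusted analysis of a morbidity outcome is stated.

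The baseline data listed under Data collection include demographic and clinical items, TIMI and GRACE scores, and "laboratory test results, ECG, echocardiographic, coronary angiographic, revascularisation and discharge medication data".

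**The concern.** Treatment is not allocated at random, so the four groups may differ at entry, including in how many patients arrive with heart failure or atrial fibrillation. A patient who has the condition on admission is more likely to be recorded with it later, either because it persists or because such patients are more prone to further episodes. A chi-square test on follow-up counts does not use admission status, so it attributes an entry difference to the strategy.

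This touches a stated aim. The Background anticipates similar one-year mortality and morbidity across strategies, and the abstract says that the comparison may guide clinicians. The limitations paragraph concedes unmeasured confounders only. Admission status of the same condition is a measured confounder, or can be derived from data that the plan already collects.

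**Working it through.** The article gives no rate of heart failure, angina or arrhythmia by strategy, so there is no figure of its own to reproduce. What follows is an illustration. Only the sample size comes from the document.

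**Inputs**
- Group size: 355 / 4 = 88.75, taken as n = 89. The 355 is from the sample size section; equal groups are an assumption.
- b, the proportion with heart failure on admission: 15% versus 35%; milder case 20% versus 30% (assumed).
- q, the probability that a patient with heart failure on admission is counted at follow-up: 65%, range 50% to 80% (assumed).
- r, the probability of new onset in the others: 8% (assumed).
- q and r are the same in both groups, so the strategy has no effect.

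**Counted rate** = b·q + (1 − b)·r
- b = 0.15: 0.0975 + 0.0680 = 0.1655
- b = 0.35: 0.2275 + 0.0520 = 0.2795
- b = 0.20: 0.1300 + 0.0640 = 0.1940
- b = 0.30: 0.1950 + 0.0560 = 0.2510

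**Chance of p < 0.05** (two-sided, normal approximation to chi-square without continuity correction). With d the difference and p̄ the mean of the two rates, s0 = √(2p̄(1 − p̄)/n) and s1 = √((p1(1 − p1) + p2(1 − p2))/n). The chance is Φ((d − 1.96·s0)/s1) + Φ((−d − 1.96·s0)/s1).
- 16.55% versus 27.95%: d = 0.114, s0 = 0.0623, s1 = 0.0618. The first term is Φ(−0.13) and the second is negligible, giving about 0.45.
- 19.4% versus 25.1%: d = 0.057, s0 = 0.0623, s1 = 0.0622. Φ(−1.05) + Φ(−2.88) is about 0.15.
- Equal b: d = 0, giving 0.05.
- 15% versus 35% with q = 50%: 14.3% versus 22.7%, about 0.30.
- 15% versus 35% with q = 80%: 18.8% versus 33.2%, about 0.59.

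Simulating the chi-square directly gives the same results to within about half a percentage point.

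**If only new events are counted.** The formula still applies, with q read as the risk of a new episode in patients who had the condition on admission. Taking q = 24% and r = 8% (assumed, a threefold risk), b = 0.15 gives 0.036 + 0.068 = 10.4% and b = 0.35 gives 0.084 + 0.052 = 13.6%. Here s0 and s1 are both about 0.0487, and the chance is Φ(−1.30) + Φ(−2.62), about 0.10. The distortion is smaller than under the prevalence reading but still twice the nominal 5%.

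**The case against.** The strongest reply is that the article contains no rule to count pre-existing disease. A reader might infer that a patient admitted in heart failure who still has it is an outcome case at all four time points. The text does not say so. The Background speaks of event rates, the Data collection section asks whether outcomes of interest occurred, and follow-up starts on the first day after hospitalisation. Baseline items and the telephone questionnaire are in Appendices B and C, which are not shown and may define the outcomes. This stands: the missing qualifier is an ambiguity, not a demonstrated counting error. Nor is it a contradiction that heart failure is both an admission predictor of death and a later outcome.

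A reader might also extend the point to left ventricular measurements and ask for analysis of covariance on the baseline echocardiogram. The article does say "An experienced research sonographer will perform standardised echocardiograms during the outpatient clinic visits three months and one year after the index discharge", but no objective compares those measurements between strategies. Nor does the article say whether the baseline echocardiogram precedes reperfusion; if it follows, adjusting for it could remove part of a treatment effect. The documents do not support that extension.

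Two further replies carry weight. Counting angina only in patients free of it at the index event would clash with the inclusion criteria, which require ischaemic symptoms. And all rates in the illustration are chosen; with equal admission rates the comparison is not distorted.

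What these replies do not remove is the stated method. The article fixes an unadjusted test for categorical comparisons between groups and ties multivariable modelling to mortality. The general caveat on observational data covers unmeasured confounders, not this one.

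**Conclusion.** The point holds as a weakness in the stated between-strategy analysis of morbidity and is worth correcting. It rests on four features of the text: groups that are not randomised, patients who may enter with the condition, outcomes not limited to new or worsening disease, and an unadjusted test as the only one stated for categorical variables.

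Under the assumed inputs, the chance of a false difference between two groups of 89 is about 45% for 15% versus 35% on admission (30% to 59% over the persistence range), about 15% for 20% versus 30%, and 5% when the groups start equal. Those figures suppose that persisting disease is counted. If only new events count, the example gives about 10%. The actual size depends on the admission imbalance between strategies, which the document does not give.

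The all-cause mortality objective is not affected.

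**What to change.** In the Statistical analysis section, make between-strategy comparisons of heart failure and arrhythmia outcomes conditional on status of the same condition before reperfusion, by regression adjustment or stratification, using the admission clinical and ECG data. Pre-reperfusion status matters because a condition that appears afterwards may itself reflect treatment. Label the unadjusted chi-square results as descriptive.

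In the secondary objectives, state that new-onset or worsening cases are reported separately from persisting pre-existing disease. Worsening needs its own category, so that patients who enter with the condition are not lost from the outcome. For angina, take history before the STEMI as the baseline, not the index ischaemic symptoms. If Appendices B and C already make this distinction, a cross-reference is enough for this part.

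The cost is a little more analysis. Where events are few, the model can carry few covariates, so admission status of the same condition should come first. This adjustment removes one measured source of imbalance; other differences between the groups remain, and the existing caveat on unmeasured confounding should stay.

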Facilitated PCI refers to routine early PCI < 12 h after reperfusion with either fibrinolysis or glycoprotein IIb/IIIa (GPIIb/IIIa) receptor inhibitors, regardless of the pharmacologic reperfusion outcome [20]. The Strategic Reperfusion Early After Myocardial Infarction (STREAM) study has shown that adopting a pharmaco-invasive strategy (i.e., fibrinolysis followed by coronary angiography or possible rescue PCI ≥ 2 h after failed fibrinolysis) offers similar benefits in all-cause thirty-day mortality when compared with primary PCI [21]. A pharmaco-invasive approach is safer and has less risk of 30-day mortality, non-fatal re-infarction, stroke, and major bleeding than facilitated PCI and fibrinolytic therapy alone (Odds Ratio for death 0.79, 95% CI 0.59–1.08; p < 0.14 when compared to fibrinolysis) [20]. Revascularisation using either thrombolysis or a pharmaco- invasive approach is common in low-to-middle-income countries (LMIC).

The Minimising Adverse Haemorrhagic Events by Transradial Access site and systemic Implementation of AngioX: Radial vs. Femoral (MATRIX: Radial vs. Femoral) randomised controlled trial has provided robust evidence in morbidity and mortality benefits that favour the radial approach as the default vascular access site in ACS patients who undergo PCI [22]. This study showed that for the invasive management of ACS, when compared to femoral access, radial access significantly reduces the net adverse clinical events mainly through a decrease in.

major bleeding and all-cause death (Hazard ratio 0.83; 95% CI 0.74–0.96; p = 0.0092 and Hazard ratio 0.72; 95% CI 0.53–0.99; p = 0.045, respectively).

Finally, sustained optimal primary and secondary prevention therapy reduces thirty-day and one-year mortality in ACS patients. Dual antiplatelet therapy (DAPT) (i.e., a combination of aspirin and P2Y12 inhibitors such as clopidogrel, ticagrelor or prasugrel) is recommended for all STEMI patients. DAPT, oral beta-blockers and angiotensin-converting enzyme inhibitors decrease all-cause mortality after a STEMI [23]. High-intensity statins significantly reduce ischaemic stroke events in STEMI patients [24]. These agents prove most beneficial when initiated early in patients with no contra-indications.

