### Study design and setting

The study is a single-centre, observational, prospective cohort of all consecutive individuals with an acute STEMI diagnosis presenting to the CMJAH. The study will take place in the division of cardiology at the CMJAH, a academic state-owned tertiary PCI-capable healthcare facility in Johannesburg, South Africa. Participants will be followed over one year, and clinical outcomes will be measured at 30 days, three months, six months and one year from the index date of hospital discharge. The first day after hospitalisation will be considered day one of the follow-up.

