This study has several potential limitations. First, it is a single-centre study and thus prone to selection bias. Second, its observational nature may not allow us to control for unmeasured confounders that may contribute to the clinical outcomes observed. Third, although participants’ and participants’ next of kin’s cellphone numbers will be recorded, the prospective nature of the study makes it susceptible to loss to follow-up. Fourth, the follow-ups will be conducted through structured telephonic interviews, which may lead to patients omitting vital health data and, thus, under-reporting adverse cardiovascular events of interest to this study. Finally, the study site’s emergency department was not fully functional due to a fire incident that occurred prior to the start of the study, which may limit the number of participants presenting at our facility.

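### Planned repeat revascularisation is pooled with unplanned in an outcome compared between reperfusion groups, so the groups can differ by treatment pathway alone

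*Protocol article*

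**What the plan says.** All references are to the protocol article.

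- **Outcome.** In Study aims, the first secondary objective is to determine the rates of a list of events, including heart failure, angina, major bleeding and thromboembolism. The list ends with "planned or unplanned repeated revascularisation at 30 days, three and six months and one year after the index STEMI". Planned and unplanned procedures form one item.
- **Comparison.** A later secondary objective is "To compare the clinical outcomes between STEMI patients who received thrombolysis, PCI, a pharmaco-invasive strategy and those who underwent no reperfusion", at the same four time points.
- **Revascularisation is among the compared outcomes.** The Background gives an event list that ends in revascularisation and continues: "We seek to compare these clinical outcomes between four primary STEMI sub-groups".
- **How the result will be read.** The Background hypothesis is that the therapies "would offer similar one-year all-cause mortality and morbidity benefits, irrespective of the revascularisation strategy used". It names fibrinolysis, primary PCI, and fibrinolysis followed by PCI.
- **Start of follow-up.** Study design and setting measures outcomes from discharge: "The first day after hospitalisation will be considered day one of the follow-up".
- **Test.** Statistical analysis uses the chi-square test for categorical variables and states: "For all tests, a p-value < 0.05 will be considered statistically significant".

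The text shown does not separate planned from unplanned procedures for the group comparison, and does not leave planned ones out of it.

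**The concern.** Unplanned repeat revascularisation usually signals that ischaemia has recurred or that the first treatment was insufficient. A planned procedure signals what the team decided to do, and that decision is tied to the strategy the patient received. The groups here are defined by strategy, so part of the outcome reflects group membership.

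A significant difference could then come entirely from scheduling. A null result would be just as hard to read, because more planned procedures in one group could offset more unplanned ones in another. Either way, the pooled rate does not answer the morbidity question in the hypothesis. This is a definition the article states, not a detail it leaves out.

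**Working it through.** The article gives no revascularisation rate, so there is no stated figure to reproduce. The check asks how far the pooled definition alone can produce a difference between groups.

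**Inputs from the article.** Minimum sample size 355 (Study sample size calculation); four groups (Study aims); chi-square test at 0.05 (Statistical analysis).

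**Assumptions, not in the article.**
- Equal groups: 355/4 = 88.75, taken as 89, 89, 89 and 88.
- Unplanned rate u = 6% in every group, so true unplanned morbidity is identical.
- Planned rate s = 5%, 10% or 15% in the groups that have planned procedures, and zero in the others.
- Planned and unplanned procedures are independent.

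**Pooled rate.** A patient counts if either type occurs: p = 1 − (1 − u)(1 − s) = 0.06 + 0.94s.

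- s = 5%: 0.06 + 0.047 = 10.7%; ratio to 6% is 1.78
- s = 10%: 0.06 + 0.094 = 15.4%; ratio 2.57
- s = 15%: 0.06 + 0.141 = 20.1%; ratio 3.35

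With unplanned procedures only, the ratio is 1.0 in each case.

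**Chance of p < 0.05.** Simulated 4 × 2 chi-square test with 3 degrees of freedom, 20,000 replicates:

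| Groups with planned procedures | s = 5% | s = 10% | s = 15% |
|---|---|---|---|
| None | about 5% | about 5% | about 5% |
| One | 21% | 60% | 88% |
| Two | 23% | 68% | 94% |
| Three | 16% | 48% | 81% |
| All four, equally | about 5% | about 5% | about 5% |

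A repeat with 200,000 replicates agreed to within about one percentage point (for example 47% in place of 48%).

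**A two-group version** with 89 per group, u = 5%, and planned procedures in one group only: s = 5%, 10% and 20% give pooled rates of 9.8%, 14.5% and 24.0%, and p < 0.05 in 23%, 57% and 96% of studies. With u = 10% the figures are 15%, 40% and 87%. A higher unplanned rate weakens the effect but does not remove it.

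The false signal depends on planned procedures being unevenly spread over the groups. The first and last rows of the table show that it disappears when they are absent or evenly spread.

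**The case against.** **Direction.** A reader might infer that the PCI-based groups are penalised, because follow-on procedures would be scheduled mainly in them, and that the no-reperfusion group would look favourable. The article does not support this. It never says which groups have planned procedures. It also treats thrombolysis as a form of revascularisation ("Revascularisation using either thrombolysis or a pharmaco- invasive approach is common in low-to-middle-income countries (LMIC"), so a planned PCI after thrombolysis could count as a repeat and load the thrombolysis group instead. For patients with no reperfusion it is unclear what a repeat would be, and the quoted hypothesis does not include that group. This objection stands: the direction is open.

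**The simulation assumes the imbalance it detects.** This is correct. The percentages show what uneven planned procedures would do. They are not evidence that the procedures will be uneven, which is why the even-spread result is given beside them.

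**Adverse-event label.** A reader might infer that the plan formally scores a planned procedure as treatment failure. It does not. The objective only asks for rates, and no composite is defined. The Discussion's phrase, "under-reporting adverse cardiovascular events of interest to this study", is a general remark about telephone follow-up. Still, the item sits in a list of adverse outcomes, and the comparison is read as morbidity.

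**In-hospital procedures.** Follow-up starts after discharge, so planned procedures completed during the index admission arguably drop out. This narrows the problem to planned procedures after discharge. It also makes counting depend on when a procedure is scheduled.

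**Separate recording may exist.** Appendices B and C are not shown and may hold the two types apart. It therefore cannot be said that the data field is missing. Separate recording would not by itself change the compared outcome as it is worded.

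**Conclusion.** The point holds as a flaw in the definition of one secondary outcome. Pooling planned with unplanned repeat revascularisation, and comparing the result between strategy-defined groups, allows a difference that says nothing about unplanned events.

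If planned procedures are concentrated in some groups, the effect can be large: under the assumed rates, a nominal 5% test rejects in 16% to 94% of studies, depending on how many groups have planned procedures (one to three) and how common they are. If they are spread evenly, there is no inflation. The real rates, group sizes and spread are unknown, so neither the size nor the direction in this study can be stated.

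The primary outcome of all-cause mortality, the survival and Cox analyses of mortality, and the sample size are untouched. The change is worth making because it is cheap and the comparison is hard to interpret without it.

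**What to change.** 1. For the comparison between reperfusion groups, define the outcome as unplanned (ischaemia-driven) repeat revascularisation after discharge.
2. Report planned procedures separately by group as a description of care, without counting them as events. The overall rate, both types together, can still be given descriptively for the whole cohort.
3. State what 'repeated' means for patients who had thrombolysis only and for those who had no reperfusion, including whether a first PCI after discharge counts.

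The cost is a short change to the outcome definition. If the case report form does not already separate the two types, it also needs one REDCap field, completed from the follow-up calls and the hospital records that the investigator already consults at re-admission. The drawback is fewer events, and so less precision, in the compared outcome.
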